### Ethics and dissemination

The institutional review board of our hospital approved all study procedures, and the study was registered with Clinical Research Information Service of Republic of Korea (KCT0008291). The trial participants and institutional review board will be notified if significant changes are made to the study protocol. During the study, participants’ personal information will only be accessible by the qualified investigators. The trial results will be published in the journal, and the report of results will be posted on the funding institute’s site (accessible to the public, participants, and healthcare professionals).

## Discussion

In this research proposal, we describe a single-center, randomized clinical trial comparing resistance exercise plus nutritional support in patients with OS in Daejeon, Korea. In this trial, we aim to determine the effects of resistance exercise and nutritional support on the SMI and BMD of postmenopausal females with OS. Functional assessment (including the grab strength test, BBT, and SPPB) and micro-architectural assessment of bone and muscle (including the CTX and whole-body phase angle) will be included in this trial, making the conclusion from this trial more clearly.

Research regarding the non-pharmacological management of OS has been published in the past. The FrOST study evaluated the effects of HI-RT and protein supplementation for about 18 months; they observed significant positive effects on the SP Z-score, and BMD at the lumbar spine and total hip [15]. However, the inclusion of only males, and differences in protein intake between the intervention and control groups, were the limitations of the study. Banitalebi et al. [41] reported the effect of elastic band resistance training in female patients with osteosarcopenic obesity. They included 63 females, and performed 12 weeks of elastic band resistance training, resulting in improvements in the osteosarcopenic obesity Z-score, 30-s chair raise test, and hand grip strength test; no improvements were observed in CTX, gait speed, and BMD. However, the intensity of resistance training was only determined by the resistance of the elastic band, and the relatively short training duration may have been an obstacle against proving the conclusion of the trial.

In this trial, we will attempt to prove the long-term effects of resistance training (24 weeks) and nutritional support (protein, vitamin D, and calcium) in females with OS. HI-RT will be applied, and the concept of the nRM/RM will be applied during the intervention [21]. Additionally, the same amount of protein, vitamin D, and calcium will be prescribed in both the intervention and control groups.

Nowadays, micro-architectural assessment of bone and muscle metabolism is commonly used in clinical practice. For example, bone turn over markers such as osteocalcin, CTX, and bone-specific alkaline phosphatase are used to monitor the effect of management in osteoporosis [42]. Fathi et al. also revealed that CTX was associated with OS in the multivariable logistic regression model (OR=4.363, 95% CI: 1.389–15.474). Likewise, phase angle analysis using BIA reflects muscle quality, and is used to detect SP [25]; additionally, these values could reflect the effect of resistance training in older patients [43]. Therefore, utilizing these assessments to evaluate the micro-architectural status of bone and muscle in participants could demonstrate the more explicit effects of the intervention.

The psychological aspects of patients with OS have not been well established. Huo et al. [6] performed a cross-sectional study of 679 participants and concluded that patients with OS exhibited more depressive symptoms than other comparative groups. However, to our knowledge, assessment of the psychological status and management of depressive symptoms in patients with OS have not been studied. Resistance exercise is well known to significantly reduce depressive symptoms among adults [44]. Therefore, in this trial, we could evaluate the psychological assessment and improvement due to the intervention, with the aim of eventually using the data to improve the non-pharmacological management and provide more clinical benefits to patients with OS.

There are several limitations to the protocol of this randomized trial. Firstly, we only included post-menopausal women residing in the community who volunteered as potential participants. This approach might be perceived as convenience sampling, despite the subsequent proper group randomization following informed consent. This introduces a potential source of bias in the study. Secondly, the sample size for this randomized trial is around 34 post-menopausal patients with osteosarcopenia. Despite the calculated estimated sample size from previous reports [14], the small sample size could reduce the statistical power.

In conclusion, this randomized trial will demonstrate the benefits of resistance exercise and nutritional support on bone and muscle health in female patients with OS, and provide long-term follow-up data.

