## Abstract

**Background:**

Osteosarcopenia is geriatric syndrome defined as the concomitant occurrence of osteopenia/osteoporosis, and sarcopenia. Osteosarcopenia is a relatively new concept in geriatric medicine; however, it may increase the risk of fragility fractures, several morbidities and mortalities, and socioeconomic costs. Although resistance exercises and nutritional support—including protein, calcium, and vitamin D—are potential non-pharmacological management procedures, evidence is still lacking. The objective of this study was therefore to evaluate the effect of combined resistance exercise and nutritional support on the quality and quantity of bone and muscle in postmenopausal females with osteosarcopenia.

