### Nutritional supplementation

Basal nutritional surveys using 24-hour recall methods will be performed in both groups (exercise and control groups) by a trained dietician. Total calorie and protein intake will be assessed, and the Mini Nutritional Assessment-Short Form at T0 (0 weeks)—with the score ranging from 0–14 points—will be evaluated to assess the nutritional status of participants [22].

Protein supplementation during resistance exercises is known as significantly increasing the muscle size and strength in healthy adults [23]. In our study, two packs of protein complex powder (Selex core-protein; protein: 20 g [50% casein + 40% whey + 10% soy, total leucine: 3000 mg], vitamin D: 800 IU [20 µg], calcium: 300 mg, fat: 1.1 g, carbohydrate: 2.5 g; Maeil Dairies Co., Ltd., Seoul, South Korea) will be provided in daily basis; therefore, a total of 40 g of protein, 1600 IU of vitamin D, and 600 mg of calcium will be provided for the 24-week program in all participants, regardless of allocated group.

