### Primary outcome measurement

The primary outcomes of this trial will be changes in the SMI and BMD of the lumbar spine and total hip using DXA (Hologic, Marlborough, Massachusetts, USA) analysis from the baseline to end of intervention (24 weeks). Changes in body composition will be repeatedly measured at T0 (0 weeks), T2 (12 weeks), and T4 (24 weeks) to evaluate the effects of resistance training and nutritional support, as well as whether the effect gain by the intervention is maintained after training (Fig. 4).

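### The objective and conclusion claim effects of nutritional support, but both arms get the same supplement, so the trial tests only added supervised resistance training; a lesser query concerns the maintenance claim.

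*Protocol article*

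**What the plan says.** **Objective and conclusion.** The Abstract (Background) gives the objective as "to evaluate the effect of combined resistance exercise and nutritional support on the quality and quantity of bone and muscle". The Background section closes with a similar aim, naming exercise and nutrition together as the intervention. The Discussion repeats it ("we aim to determine the effects of resistance exercise and nutritional support on the SMI and BMD"), adds "we will attempt to prove the long-term effects of resistance training (24 weeks) and nutritional support (protein, vitamin D, and calcium", and ends by saying that "this randomized trial will demonstrate the benefits of resistance exercise and nutritional support on bone and muscle health".

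**Treatment in each arm.** Under Nutritional supplementation, two packs a day of the protein powder "will be provided for the 24-week program in all participants, regardless of allocated group". The Abstract (Methods) and the Discussion confirm that the amounts are equal in the two arms. Under Exercise protocol, the intervention group trains in the hospital gym twice a week for 24 weeks. Controls receive a brochure and are encouraged to exercise at home.

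**Analysis.** The Statistical analysis section compares change from baseline to the end of the intervention between the two groups, by t-test or Mann-Whitney U test. Secondary outcomes are modelled by group and time.

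**Maintenance.** Under Primary outcome measurement, body composition is measured at T0 (week 0), T2 (week 12) and T4 (week 24), partly to see "whether the effect gain by the intervention is maintained after training". The last sentence of the Discussion says the trial will "provide long-term follow-up data".

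**The concern.** A randomised trial can attribute to treatment only what differs between its arms. Here the supplement does not differ, so a claim about nutritional support, alone or as part of a package, has no randomised evidence behind it. The objective nevertheless makes that claim, and the conclusion announces it in advance.

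The Abstract says the results are meant to feed into guidelines for non-pharmacological management. A positive result reported under the present objective could be taken as support for exercise plus nutrition, when only the exercise part was tested. A null result could be taken to mean that the combination failed, when both arms had received half of it.

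The maintenance sentence raises a smaller question of the same kind. Persistence after training needs a measurement taken some time after training stops, and the three time points listed do not include one.

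**Working it through.** **1. What the sample size was built for.** The Sample size calculation section takes SMI changes of -0.03 (SD 0.21) in controls and 0.30 (SD 0.22) with intervention.

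- Pooled SD = √((0.21² + 0.22²)/2) = 0.215
- d = (0.30 − (−0.03))/0.215 = 0.33/0.215 = 1.53, as stated
- A two-sided t-test at 5% with 95% power needs 12.1, so 13 per group, as stated (power 96.3% at 13)

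The trial is thus sized for a single between-arm difference, which is also what the primary analysis tests.

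**2. What differs between the arms.**

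| Component | Intervention | Control | Difference |
|---|---|---|---|
| Protein per day | 2 × 20 = 40 g | 40 g | 0 |
| Vitamin D per day | 2 × 800 = 1600 IU | 1600 IU | 0 |
| Calcium per day | 2 × 300 = 600 mg | 600 mg | 0 |
| Home-exercise brochure | yes (read as given to all participants) | yes | none intended |
| Supervised gym training | twice weekly, 24 weeks | no | the contrast |

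**3. What the contrast estimates.** Let E = 1 for supervised training and N = 1 for supplement, and write

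mean change = b0 + bE·E + bN·N + bEN·E·N,

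where b0 holds everything common to both arms (time, home exercise, regression to the mean).

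- Control (E = 0, N = 1): b0 + bN
- Intervention (E = 1, N = 1): b0 + bE + bN + bEN
- Difference: bE + bEN, the effect of training in women who all take the supplement
- Package against no package: bE + bN + bEN, which exceeds the contrast by bN

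The term bN cancels from the difference. Even without the interaction, the arm-level rows for (intercept, E, N) are (1, 0, 1) and (1, 1, 1), a matrix of rank 2 for 3 parameters. Nutrition cannot be separated from the intercept. More participants would not change this, because no arm has N = 0.

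**4. Could within-arm change fill the gap?** The control arm's mean change is b0 + bN. It mixes the supplement with home exercise, the passage of time and regression to the mean, the last because the eligibility criteria select women for low muscle and bone values. It cannot be read as a nutrition effect.

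**5. Timing of the last measurement.** Training lasts 24 weeks and T4 is at 24 weeks, so 24 − 24 = 0 weeks of post-training observation for DXA. The other stated schedules agree: CTX ends at T4, phase angle runs to the end of the intervention, and adverse-event screening stops there. The readable text names no later visit.

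**The case against.** **The equal supplementation is deliberate and sound.** The Discussion names unequal protein intake between arms as a limitation of the earlier trial in men, and this trial removes it. The Abstract (Methods) states openly that both groups get the supplement and only one trains. All of this stands. A reader might infer that the design is faulty. It is not: it isolates exercise well. But having taken nutrition out of the contrast, the article cannot also claim its benefit.

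**The objective may mean exercise on a nutritional background.** The design overview can be read that way. The closing claim of benefit from both components cannot.

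**Usual care is never mentioned.** A reader might infer that the objective promises a comparison with usual care. The article names no such comparator. The supported statement is only that the combined package is not compared with its absence.

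**No within-arm test for nutrition is planned.** Correct: the planned analyses are between groups. The risk lies in how results are reported under the present objective, and misreading is a possibility rather than a certainty.

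**A later visit may exist.** A reader might infer that the trial has no post-training assessment at all. The documents do not settle this. Fig. 4, cited with the maintenance sentence, is not shown. Recruitment ends in November 2023 and completion is estimated for December 2024. A woman enrolled on 30 November 2023 would finish 24 weeks in mid-May 2024, about seven months before completion. That interval could hold a further visit, or only analysis.

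**Long-term may mean 24 weeks.** The Discussion attaches the term to the 24-week training itself, after calling a 12-week programme relatively short. The closing phrase may therefore mean no more than the 24-week data. This softens that phrase, but not the statement about maintenance after training, which occurs only under Primary outcome measurement and is no part of the objective.

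**Conclusion.** The main point holds with high confidence. The stated objective and conclusion go beyond what the randomised comparison can show. The between-arm difference in supplement is zero, so the trial gives no randomised estimate of the effect of nutritional support or of the package against no package. It does validly estimate the added effect of supervised progressive resistance training over 24 weeks. This rests on the supplement being provided equally, as stated in three places, and on home-exercise advice being common to both arms. If only controls received the brochure, the contrast would be supervised training against home-exercise advice, and the conclusion about nutrition would be the same.

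The maintenance point holds only as an inconsistency in the readable text: the three listed time points end when training ends, so they cannot show persistence afterwards. Whether a later visit is scheduled cannot be determined without Fig. 4.

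The fault is in the claims. Design, sample size and planned between-group analysis are unaffected by it.

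**What to change.** 1. Restate the objective (Abstract, end of Background, Discussion) and the planned conclusion as the effect of adding supervised progressive resistance training to nutritional supplementation plus home-exercise advice over 24 weeks, in postmenopausal women with osteosarcopenia.
2. State that within-arm changes from baseline are descriptive and will not be attributed to nutrition.
3. Reconcile the maintenance sentence under Primary outcome measurement, and the follow-up phrase closing the Discussion, with the schedule in Fig. 4. If a post-training assessment exists, name it and its timing. If not, drop the maintenance claim and describe the data as 24-week, end-of-intervention data.

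The cost is wording only, and a narrower claim. Recruitment, visits, sample size and analysis do not change.

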## Trial status

Protocol version number V1.0, 07 March 2023. The institutional review board of our hospital approved all study procedures, and the study was registered with Clinical Research Information Service of Republic of Korea (KCT0008291). Patient recruitment began in March 2023, and the completion date for recruitment is in November 2023. The experiments are currently in progress, with the estimated date of completion set for December 2024.

## Data Availability

Not applicable.

## Abbreviations

BBT: Berg Balance Test
BDI: Beck Depression Inventory
BIA: Bioelectrical Impedance Analysis
BMD: Bone Marrow Density
BMI: Body Mass Index
CTX: C-telopeptide (type 1 collagen)
DXA: Dual-energy X-ray Absorptiometry
HI-RT: High-intensity Resistance Exercise
MQI: Muscle Quality Index
nRM: Non-repetition Maximum
OS: Osteosarcopenia
PHQ-9: Patients Health Questionnaire-9
RCT: Randomized Controlled Trial
RM: Repetition Maximum
SMD: Standardized Mean Difference
SMI: Skeletal Muscle Index
SP: Sarcopenia
SPPB: Short Physical Performance Battery
